### Data management

All outcomes will be entered into OpenClinica Community software (Version: 3.12.2, OpenClinica LLC and collaborators, Waltham, MA, USA, www.OpenClinica.com.), an online password protected electronic data capture system. Data will be collected anonymously. A source document review of randomly selected subjects will take place to ensure correct entering of data. All paper files will be preserved for at least 15 years.

### Statistical analysis

The primary outcome is the difference in KOOS pain subscale change from baseline to 4 months between both groups. Repeated measurements regression analysis for continuous variables will be performed, based on intention to treat analysis to determine a difference between groups. Generalized estimating equations (GEE) will be used to enable inclusion of all available measurements in the regression models even if they are correlated. It also allows us to adjust for unequal distribution of prognostic variables over the two groups, which easily can occur in smaller randomized clinical trials. Radiographic severity, pain pressure threshold, and degree of sensitized pain according to painDetect will all be tested for equal distribution and, if more than 10% different, we will test if this variable changes the estimate with more than 10%. If this is the case, the variable will be included in the adjusted analysis. The adjusted analysis will be the primary analysis, but we will also present the unadjusted analysis. If some of the patients do not receive the treatment as allocated, we will also perform a per protocol analysis where the patients that did not comply with the allocated treatment will be excluded. Repeated measurement regression analysis will also be used for all continuous secondary outcomes: KOOS subscales, VAS, ICOAP, painDETECT, EQ-5D-5L, and PPT scores.

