### Outcome measurements

Outcome measurements will be recorded at baseline and 1, 4, 8, and 12 months after the procedure. The primary outcome is change of the knee injury and osteoarthritis outcome score (KOOS [14]) pain subscale score between baseline and 4 months follow-up. Secondary outcomes are the change of pain subscale score between baseline and 1, 8, and 12 months. Other secondary outcomes are the change of the remaining dimensions of the KOOS (symptoms, daily living, sport and recreation and quality of life), additional questionnaires, and the pressure pain threshold after 1, 4, 8, and 12 months.

Changes on MRI will be compared between baseline and after 1 and 4 months. All clinical trial study activities are summarized in Table 1.

**Table 1 Tab1:** Clinical trial study activities overview

	Study period						
	Enrolment/baseline	Intervention	Post-allocation				Close-out
Timepoint**	***− 2 weeks***	0	***Post-intervention***	***1 month***	***4 months***	***8 months***	***12 months***

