### Sample size calculation

Calculations are partly based on the previous observational studies by Okuno et al. [6, 7]. Despite a possible placebo effect, which account for effect sizes up to 0.5 [21], they found effect sizes of > 5. For our study, we assumed we would require to demonstrate a large effect size of > 0.8 (strong effect) compared to sham embolization since GAE still is (minimally) invasive. Assuming this projected effect size of 0.8, and a standard deviation of 16 for the KOOS (100-0) pain score (estimated from multiple OA studies at Erasmus MC), beta of 0.80, and alpha of 0.05, 48 patients (*n* = 24 per study arm) are required to detect an increase (higher scores indicate less pain) in primary outcome measure of 8 points in the control group (placebo effect) compared to 21 points in the intervention group. The targeted sample size will be 58 to account for approximately 20% of patients lost to follow-up. We also expect a more homogeneous study population since all included subjects have an NRS pain score ≥ 4 and ≤ 8. With this sample size, and in case of lower variation in pain scores than SD of 16, we expect we could also detect smaller effect sizes between 0.5 (moderate effect) and 0.8.

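### Baseline KOOS pain is not among the named adjustment variables and no baseline term is stated, so precision may be given away and power rests on an unstated correlation

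*Protocol article*

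**What the plan says.** The Statistical analysis section of the protocol article puts the primary outcome on the change scale: "The primary outcome is the difference in KOOS pain subscale change from baseline to 4 months between both groups". On the model it says: "Generalized estimating equations (GEE) will be used to enable inclusion of all available measurements in the regression models even if they are correlated".

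Three variables are named as candidates for adjustment: "Radiographic severity, pain pressure threshold, and degree of sensitized pain according to painDetect". Each is first compared between arms. If it differs by more than 10%, it is then checked for whether it moves the treatment estimate by more than 10%, and only then does it enter. The result of this selection carries the main inference: "The adjusted analysis will be the primary analysis, but we will also present the unadjusted analysis".

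Baseline KOOS pain is not in that list, and the section does not say how the baseline score enters the GEE. The score is available: "Outcome measurements will be recorded at baseline and 1, 4, 8, and 12 months after the procedure", and Table 1 schedules the KOOS questionnaire at enrolment.

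The Sample size calculation section plans for gains of 21 points (GAE) and 8 points (sham), using "a standard deviation of 16 for the KOOS (100-0) pain score". It gives no SD of change and no correlation between baseline and month 4.

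**The concern.** The stated reason for adjusting is that prognostic variables can be unevenly distributed in a small trial. The baseline value of the outcome is the obvious variable for that reasoning, since it enters the change score directly. As written, a chance imbalance in pressure pain threshold can trigger adjustment, while a chance imbalance in baseline KOOS pain triggers nothing.

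Two things are at stake. The first is precision: a change-score comparison has a variance at least as large as a baseline-adjusted one, and with about 24 evaluable patients per arm the difference can be material. The second is the basis of the power statement: the effect is a difference in change, but the SD is described as that of the score. The two SDs agree only at one particular correlation.

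**Working it through.** **Inputs.** From Sample size calculation: difference 21 − 8 = 13 points; SD 16; alpha 0.05 (taken as two-sided, which reproduces the plan's number); power 0.80; 24 per arm. Assumed, because the article does not give it: the correlation r between baseline and month-4 KOOS pain, shown at 0.3, 0.5 and 0.7.

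**1. The plan's own figure.** n per arm = 2 × (1.96 + 0.842)² × 16² / 13² = 2 × 7.85 × 256 / 169 ≈ 23.8, so 24 per arm and 48 in total. This reproduces the plan. Power at 24 per arm is 80.4% by the normal approximation and 78.7% by the t-test. The match requires 16 to be the SD of the quantity analysed.

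**2. SDs of the two analyses**, if the score has SD 16 at both visits:
- change score: 16 × √(2(1 − r)), which equals 16 only at r = 0.5 and is larger below that;
- baseline-adjusted: 16 × √(1 − r²), which never exceeds 16;
- ratio of variances, adjusted to change: (1 − r²) / (2(1 − r)) = (1 + r)/2, so adjustment removes a fraction (1 − r)/2.

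**3. Results**, 24 evaluable per arm, 13 points, t-test power (one degree of freedom deducted for the covariate):

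| r (assumed) | SD, change | SD, adjusted | Variance cut | Power, change | Power, adjusted |
|---|---|---|---|---|---|
| 0.3 | 18.9 | 15.3 | 35% | 64.4% | 82.3% |
| 0.5 | 16.0 | 13.9 | 25% | 78.7% | 88.9% |
| 0.7 | 12.4 | 11.4 | 15% | 94.5% | 97.1% |

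With 23 per arm (58 × 0.8 = 46.4 in total) the pairs are 62.5/80.6%, 76.9/87.5% and 93.6/96.5%.

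**4. Effect of the entry range.** The table keeps the baseline SD at 16. Sample size calculation expects a more homogeneous population because entry requires NRS 4 to 8. Suppose, for illustration only, that this reduces the baseline SD to 10.
- *Ordinary range restriction*, starting from r = 0.5 and SD 16 at both visits. The slope stays 0.5 and the residual variance stays 256 × 0.75 = 192. The follow-up variance is 0.25 × 100 + 192 = 217 (SD 14.7), and r falls to 0.5 × 10 / 14.7 = 0.34. The variance of change is (0.5 − 1)² × 100 + 192 = 217, so its SD falls from 16 to 14.7. Power at 24 per arm is 84.9% unadjusted against 88.9% adjusted.
- *r held at 0.3, follow-up SD 16.* The variance of change is 100 + 256 − 2 × 0.3 × 10 × 16 = 260, SD 16.1. Power at 24 per arm is 78.1% unadjusted against 82.3% adjusted.

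In both cases the gap shrinks to about 4 percentage points.

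**The case against.** **The text does not rule out baseline adjustment.** The GEE uses all available measurements, and baseline is one of the measurement times. A GEE that treats baseline as a response with a common mean across arms would recover roughly the precision of baseline adjustment, depending on the working correlation. Defining the outcome as change does not exclude adjustment either: regressing change on baseline gives the same treatment estimate as regressing follow-up on baseline. An article may also leave the exact parameterisation to the full protocol. This stands, so one cannot say that the primary analysis fails to adjust. What remains is that the article does go into detail here. It names the candidates, the entry rule and the primary analysis, and the baseline outcome is in none of them. With free arm means at baseline and a group-by-time term, the GEE is in effect a change-score comparison.

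**A reader might infer that the trial is underpowered.** The documents do not show this. The 24 per arm is adequate without adjustment (normal approximation) if r is at least 0.5, or if 16 is really an SD of change. The figure comes from in-house studies that are not shown, and it is applied to gains in score, so its meaning cannot be settled from the article.

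**A reader might infer that the NRS 4 to 8 criterion makes matters worse by lowering r.** A lower r produced by narrower baseline spread does not imply a larger SD of change; in the range-restriction example the SD of change falls and unadjusted power rises.

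**A reader might infer bias from regression to the mean.** Randomisation makes it equal in expectation in both arms. The possible loss is in precision and in protection against chance imbalance.

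Finally, the t-test stands in for the planned GEE, which retains partly observed patients, so the power figures are approximate.

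**Conclusion.** The point holds as an unstated and probably suboptimal choice. Baseline KOOS pain is absent from the named adjustment set and no baseline term is given. Unless the GEE constrains the baseline mean, the primary comparison is unbiased but no more precise than a baseline-adjusted one, and usually less.

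With SD 16 at both visits and r between 0.3 and 0.7, the avoidable variance is 35% down to 15%. The power gap at 24 per arm runs from about 18 percentage points to about 3. It is about 4 points in the two illustrations with narrower baseline spread. The correlation, the equal SDs and the reduced baseline SD of 10 are all assumptions.

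The power statement is best described as depending on an unstated correlation. Nothing here shows that it is wrong or that the choice of model decides whether the trial reaches its target. This is a free improvement, not a must-fix error.

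**What to change.** Before unblinding, state one of the following for the primary analysis, with the month-4 between-group contrast as the primary estimate:
- baseline KOOS pain as a covariate that is always included, exempt from the 10% rules, with baseline-by-visit terms in the repeated-measures model; or
- a repeated-measures model with baseline as a response and its mean constrained equal across arms.

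Do the same for each continuous secondary outcome with its own baseline value. In Sample size calculation, say whether 16 is the SD of the score or of its change. If it is the score, give the assumed correlation, or base the power statement on the adjusted analysis.

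The cost is a few sentences and the model terms. The data are already scheduled, and nothing changes for patients. Settling it before unblinding avoids the appearance of a data-driven choice.

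### The covariates of the primary adjusted analysis are chosen from the data, partly by how far they move the treatment estimate; the rule is mostly conservative and costs power if the covariates are prognostic

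*Protocol article*

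**What the plan says.** The protocol article, Statistical analysis, defines the primary comparison thus: "The primary outcome is the difference in KOOS pain subscale change from baseline to 4 months between both groups". The model is a repeated-measurements regression by intention to treat, fitted by GEE. One reason given for GEE is that it allows the analysts to "adjust for unequal distribution of prognostic variables over the two groups, which easily can occur in smaller randomized clinical trials".

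The candidates are radiographic severity, pressure pain threshold (PPT) and the painDETECT score. Each is checked for balance between the arms and, "if more than 10% different, we will test if this variable changes the estimate with more than 10" per cent. Then: "If this is the case, the variable will be included in the adjusted analysis". On status: "The adjusted analysis will be the primary analysis, but we will also present the unadjusted analysis".

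The section does not say on what scale a 10% difference is measured, and it describes no allowance for the selection.

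**The concern.** Under 1:1 randomisation a baseline difference is due to chance, and with 24 to 29 patients per arm differences of this order are routine. Imbalance is therefore a weak reason to include or drop a covariate. What makes a covariate useful is its relation to the outcome.

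The second step is the more serious one. It needs the outcome by arm, and its threshold is relative to the treatment estimate itself. A given absolute shift passes easily when the estimate is near zero and may fail when the estimate is large. The primary model is then partly a function of the effect it is meant to estimate, while its standard error is computed as if the model had been fixed.

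The scale also matters. KL grade runs from 1 to 3, and PPT is measured at four sites. Two analysts could apply the text in good faith and arrive at different primary models. At stake are the correct size of the primary interval, the precision available in a small trial, and a clear answer if the adjusted and unadjusted results disagree.

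**Working it through.** **1. The plan's own figure.** Sample size calculation section: difference 21 − 8 = 13 points, SD 16, alpha 0.05 (taken as two-sided), power 0.80.

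n per arm = 2 × (1.96 + 0.84)² × 16² / 13² = 2 × 7.84 × 256 / 169 = 23.8, so 24 per arm and 48 in total. This matches. Multiplying by 1.2 gives 57.6, so 58, as stated. The calculation is an unadjusted comparison; no covariate enters it.

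**2. How often the first step is met.** Assume KL grade is split in two, with a true proportion p of 0.3 to 0.5 in both arms. A gap above 10 points then needs a difference of at least 3 patients (3/24 = 12.5 points; 3/29 = 10.3 points). Exact binomial probability:

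- 24 per arm: 43% to 47%
- 29 per arm: 47% to 51%

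**3. Why the second step depends on the effect.** Adjusting for a covariate with correlation r and standardised imbalance d moves the estimate by about r × 16 × d. At r = 0.3 this is 4.8 × d points. If the unadjusted estimate is 13, the threshold is 1.3 points, so d must exceed 1.3/4.8 = 0.27. If the estimate is 2 (an illustrative value), the threshold is 0.2 points, so d need only exceed 0.2/4.8 = 0.04.

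**4. Effect of the whole rule.** Simulation with 24 per arm, SD 16, true difference 0 or 13, and three independent covariates each correlated r with the outcome (joint R² = 3r²). Assumed: binary KL with p = 0.5; PPT mean 40, SD 16; painDETECT mean 12, SD 6. Imbalance means more than 10 percentage points for KL, or more than 10% relative difference in means for the others. ANCOVA at 4 months stands in for the GEE. Type I error is shown as a range where repeat runs differed.

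| r (R²) | Power, rule | Power, always adjusted | Power, unadjusted | Type I error, rule |
|---|---|---|---|---|
| 0 to 0.1 (0 to 0.03) | 0.78 | 0.76 | not tabulated | 0.056 at r = 0 |
| 0.2 (0.12) | 0.79 | 0.80 | 0.79 | 0.046 |
| 0.3 (0.27) | 0.83 | 0.88 | 0.79 | 0.038 to 0.044 |
| 0.4 (0.48) | 0.89 | 0.96 | 0.79 | 0.025 to 0.028 |

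At r = 0.3 at least one covariate is selected in about 80% of trials under the null, but in 62% when the effect is 13. This is step 3 at work.

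**5. Sensitivity to the meaning of 10%.** The same design with a difference of 12.8 points (0.8 × 16) and normal covariates was run under three readings: a standardised difference above 0.1, means differing by more than 10% (coefficient of variation 0.35 assumed), and p < 0.10.

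| R² | Power, rule (range over readings) | Power, always adjusted |
|---|---|---|
| 0 | 76.5% to 77.0% | about 74% to 75% |
| 0.1 | 76.7% to 78.3% | about 78.6% |
| 0.3 | 79.0% to 84.9% | about 88% |
| 0.5 | 80.0% to 91.4% | about 96% |

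Across readings, R² and true effect, at least one covariate is selected in 11% to 98% of trials. With all three covariates always included, type I error was 4.8% to 5.2% throughout.

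**6. Why the intervals are too wide.** The rule drops a prognostic covariate when it happens to be balanced, so its variance stays in the residual although it no longer disturbs the comparison. At R² = 0.5 the mean standard error is 3.8 to 4.3, against an empirical SD of the estimate of 3.5 to 3.8.

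**The case against.** The strongest reply is that the plan is neither silent nor open-ended. It fixes the candidates, both thresholds and which analysis is primary, and it promises the unadjusted result, so any divergence will be visible. All of that stands. A reader might infer that the primary analysis is not pre-specified at all or invites free model searching; the text does not support that. What is left to the data is which of three named covariates enter.

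A reader might also infer an inflated false-positive rate. The figures do not support that either: the highest type I error seen is 5.6%, with covariates unrelated to the outcome, and it falls below 5% as they become prognostic.

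The power loss is conditional too. It is measured against always adjusting, not against the design, which assumed no adjustment; at correlation 0.3 the rule does better than the unadjusted analysis (0.83 against 0.79). The correlations are not in the document, and independence favours the criticism, since PPT and painDETECT both bear on sensitisation. With those two correlated 0.5 (assumed), the loss is about 3 points at correlation 0.3 (0.816 against 0.847) and nil at 0.2 (0.796 against 0.798). Finally, ANCOVA is not the planned GEE, so the third digit should not be relied on.

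What survives is that inclusion depends on the observed effect, that the scale is undefined, and that the protocol itself calls these variables prognostic. If that is right, the rule is the less efficient way to use them.

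**Conclusion.** The point holds as a fault in a stated rule. It is not a detail left to an analysis plan, because a plan that followed this text would carry the fault forward. The covariate set of the primary model depends on chance imbalance on an unspecified scale and on the treatment estimate, and the reported standard errors ignore this.

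Under independent covariates with ANCOVA in place of GEE, the size is: type I error about 0.04 and 0.025 at correlations of 0.3 and 0.4, with about 5 and 7 points of power lost against always adjusting; about 1 point lost at 0.2; and about 2 points in the rule's favour at 0 to 0.1. The error in size is therefore mostly in the safe direction.

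One might go further and conclude that the trial is underpowered because of the rule. It is not: 24 per arm is reproduced without any covariate. This should be corrected, but it does not put the trial's validity in doubt.

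**What to change.** Before unblinding, delete both 10% steps. State that the primary model always includes KL grade, baseline painDETECT and baseline PPT at one named knee site, whatever the observed imbalance or change in estimate. State whether KL grade enters as a linear term or as a three-level factor. Add baseline KOOS pain, unless the GEE already carries the baseline score among its repeated responses; it is not among the protocol's candidates and was not in the simulations, but the trial collects it. Keep the unadjusted analysis as supportive.

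The change is one of wording, since every variable is already measured at baseline. It uses four degrees of freedom, or five if KL grade is a three-level factor, and costs about 2 points of power if the covariates prove not to be prognostic.

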## Discussion

GAE is a novel intervention for patients with symptomatic, mild-to-moderate knee OA [6, 7]. Initial results from cohort studies show promising outcomes with up to 4 years of pain improvement but the studies lacked a control group [5]. This randomized trial is designed to determine the efficacy of this treatment compared to a sham treatment. Sham controlled surgical trials for knee OA and degenerative meniscal tear treatment have had great impact on current insight in treatment of symptomatic knee OA. Not until sham controlled studies demonstrated no difference in pain reduction between surgery and sham surgery was the procedure removed from guidelines [21, 22]. We firmly believe that, before introducing promising new treatments, these have to be evaluated against control groups. For surgical therapies, this involves the use of sham treatment.

In our initial protocol, we planned for the sham group to undergo angiography of the genicular vessels without embolization in order to visualize and compare the angiogenesis in both groups. However, after consulting with the local ethical committee, this was deemed too invasive as a sham intervention for patients who already had knee complaints and was not necessary to achieve the primary objective. Therefore, we changed the sham treatment to be an incision in the groin without a catheter entering the femoral artery. This less invasive form of a sham procedure is a challenge with regard to blinding. Patients must be under the impression that a catheter is actually entering the arteries and that the interventional radiologist is performing the procedure. Using noise-canceling headphones so patients cannot hear their surroundings, using the C-arm to mimic angiography, and giving patients in the sham group the same post procedural care as the intervention group are examples of how we maintain adequate blinding. The upside of changing the sham procedure to this less invasive method is that patients will not be exposed to any unnecessary additional risk associated with angiography. To assess whether we succeeded to keep the intervention blinded for the patient, we will ask them for their own perception of group allocation after the treatment.

Several research groups are currently evaluating the outcome of GAE. Recently, results of non-randomized pilot studies have been published showing promising results; however, the authors also state the importance of testing GAE in a randomized controlled trial [8, 9]. Because GAE shows potential but is also invasive and incurs additional costs, a thorough evaluation is warranted before being introduced into clinical practice.

We are aware of one published protocol describing a similar trial [23]. We believe that multiple trial outcomes will strengthen the evidence upon which we can draw a conclusion on the efficacy of GAE. There are some differences to the aforementioned study protocol. Using a sophisticated MRI protocol including high-resolution DCE-MRI and testing pain pressure thresholds, we aim to expand the knowledge on the working mechanism of GAE. DCE-MRI provides quantitative measures of perfusion. This can be used to monitor changes occurring due to the alteration of angiogenesis by GAE [24]. It is suggested that DCE-MRI derived parameters are more sensitive to treatment response and associate stronger with pain changes than synovial volume [25]. If pain reduction due to GAE is truly achieved through reduction of synovitis, the perfusion parameters in the synovium should decrease commensurate with clinical improvement.

